### Randomization and blinding

Participants are assigned to the intervention or control group after having given written informed consent to participate in the study. Children or adolescents, their parents, and their teachers are always assigned to the same group. A randomization list with equal proportions of both groups was generated with the software R (based on the function “sample”) [48] before the start of the study. Participants are successively assigned to one of the two groups according to the order of their recruitment (date of written informed consent) using the randomization list. Only after inclusion in the study, DigiPuR study staff look up the assignment in the randomization list and record the assignment in the coding list, which is kept locked in a cabinet and only accessible to the study management. They inform therapists about the group assignment by e-mail and participants during the technical briefing by a video or phone call or on site at the hospital. Blinding of participants, case-leading therapists, and conducting study staff is not possible due to the different nature of treatment in the two groups. Data evaluation, however, is blinded, as group allocation is coded without knowledge of the data analysts.

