#### Pre-post-follow-up assessment

Admission and discharge assessment as part of the standard hospital assessment are carried out on paper questionnaires (in exceptions where necessary online) through trained staff during the partial or full inpatient hospital stay in the period from preliminary talk to admission until 1 week after admission and in the period from 1 week before discharge until discharge (pre). For the post, follow-up 1, and follow-up 2 assessment (8, 24, and 36 weeks after discharge), the participants receive an e-mail containing a link for an online survey on the SoSci Survey platform [50], which they can respond to at home via the browser of their computer, tablet, or smartphone within 1 week. At each time point of assessment, the survey lasts no longer than about 45 min.

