#### Ambulatory assessment

The ambulatory assessment consists of daily questions about well-being, affect, sleep quality, the school situation, and social relationships that children and adolescents (30 items), the participating parent or caregiver (17 items), and, if teachers participate, a teacher (10 items), answer on their personal or a study smartphone via the app *movisensXS* [49] (see Fig. 3). The children’s and adolescents’ items are presented in written and audiovisual form, so that children who are not yet able to read confidently can have the items read aloud. Ambulatory assessment takes place every day between 5 and 9 o’clock in the evening from 2 weeks before discharge to 8 weeks after discharge and takes a maximum of 5 min per day. Teachers answer the items only on school days and have a larger time frame to respond to increase adherence by being more flexible. Children and adolescents, parents, and teachers are reminded of the daily survey by alarms and can postpone alarms three times. The data collected in the ambulatory assessment is evaluated individually on a weekly basis by summarizing all answers and preparing them graphically (see Fig. 4). The case-leading therapist can use this overview of the participants answers during the last week(s) as a basis for the next regular video call.

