**Fig. 4 Fig4:**
[figure not shown]
Sample excerpt from the weekly graphical evaluation of the ambulatory assessment data for the therapist. o data point. 

missing. Color coding for school attendance (green = yes, yellow = partial, red = no, gray = no school day)

With the start of the ambulatory assessment, all participants receive a short technical briefing, in which the app *movisensXS* [49] is installed on the participant’s Android smartphone or a study smartphone. When using their own smartphones, the participants can be reimbursed for data used for the daily surveys. After installation of the app *movisensXS* [49], all technical components of the study are briefly explained and tested: (1) the app *movisensXS* [49] with messenger function, (2) the video phone program VidyoConnect [51], (3) the university hospital’s own cloud service for the pseudonymized worksheets of the weekly goals and other therapy materials, and (4) the online platform SoSci Survey [50] for post- and follow-up surveys. Despite the intuitive and simple handling of all components, all participants receive written, illustrated instructions. For further questions or in case of technical difficulties, the study contact details (e-mail address and telephone number) are also included in the instruction.

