#### Instruments

The instruments used in DigiPuR (see Table 1) are chosen to cover the five domains (symptoms, functioning, consumer perspectives, environments, systems) of the comprehensive conceptual model of outcomes of mental health care for children and adolescents [46]. The instruments and scales used in the pre-post-follow-up assessment and the ambulatory assessment are briefly described in the following, sorted according to the five domains. Item formulations were adapted where necessary so that they are understandable and suitable for both children and adolescents. Items are only presented if their content is relevant to the respective group (e.g. items on satisfaction with the program for video calls only when it was used). Primary outcomes are number of readmissions, satisfaction with treatment, health-related quality of life, and symptom severity; all others are secondary outcomes (see Table 1). As there is a great heterogeneity of diagnoses in the patient sample, the evaluation aims to assess the reintegration phase and the well-being of patients globally and across disorders. General constructs relevant to different disorders were selected and instruments were used for comparability across the age range.

**Table 1 Tab1:** Overview of assessed outcomes, assigned domains, instruments, and raters at the different study time points

Outcome	Domain [46]	Instrument or scale	Rater	Study period				
				Enrollment	Allocation	Post-allocation		
				Admission	Ambulatory assessment (2 weeks before discharge until 8 weeks after)	Pre (discharge)	Post (8 weeks after discharge)	Follow-up (24 and 36 weeks after discharge)
Symptom severity	Symptoms	DISYPS-III SCREEN [52]	CA, P*, T*	x		x	x	x
Stress vulnerability and coping strategies	Symptoms (part 1), functioning (part 2)	Adapted from SSKJ-3-8R (parts 1 and 2) [53]	CA	x		x	x	x
Self-efficacy	Functioning	WIRKSCHUL [54], WIRKSOZ [54], WIRKLEHR [54], WIRKELTERN (self-development)	CA, P, T	x		x	x	x
Health-related quality of life	Consumer perspectives, environment	KIDSCREEN-27 [55]	CA, P*	x		x	x	x
Occupational well-being	Environment	Emotional exhaustion [56], enthusiasm for teaching [56]	T			x	x	x
Satisfaction with treatment	Consumer perspectives	Adapted from FBB [57]	CA, P, T, TH				x	
Satisfaction with technical components	Consumer perspectives	SUS [58], self-development	CA, P, T, TH				x	
Expectation of change	Consumer perspectives	Adapted from patient’s expectation of change [59]	CA, P			x		

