##### Expectation of change

Patients’ and parents’ expectation of change regarding the aftercare is assessed as a covariate with 4 thematically adapted items (e.g., “I think that through DigiPuR I will cope better with my daily life”) from the scale *Patient’s expectation of change* of the questionnaire for measuring common factors in psychotherapy (FERT; factorial reliability of the original scale with 8 items ρϲ = .94) [59].

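### Families and teachers learn their group about two weeks before discharge, so the discharge reference scores and the expectation covariate are collected after unblinding

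*Protocol article*

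**What the plan says.** All of this is in the Methods of the protocol article.

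- **Disclosure** (Randomization and blinding): the list is consulted only after inclusion. Then: "They inform therapists about the group assignment by e-mail and participants during the technical briefing by a video or phone call", or on site. The e-mail to therapists has no date beyond being after inclusion.
- **Briefing** (Ambulatory assessment, text after Fig. 4): "With the start of the ambulatory assessment, all participants receive a short technical briefing".
- **Ambulatory assessment**: it runs daily "from 2 weeks before discharge to 8 weeks after discharge".
- **Discharge questionnaire** (Pre-post-follow-up assessment): it is completed "in the period from 1 week before discharge until discharge (pre"). Table 1 lists this time point under the post-allocation heading and admission under enrollment.
- **Expectation** (Expectation of change): "expectation of change regarding the aftercare is assessed as a covariate with 4 thematically adapted items". The sample item is "I think that through DigiPuR I will cope better with my daily life". Table 1 marks it once, at discharge, for patients and parents.
- **Use of the scores** (Hypotheses; Statistical analyses): quality of life and symptom severity are hypothesised to develop better over pre, post and follow-up. They are tested by the group-by-time interaction in a mixed ANOVA.

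**The concern.** The article explains the lack of blinding by the different nature of the two treatments. That covers the aftercare, which starts after discharge. It is no reason to reveal the group before the last measurement that precedes the aftercare.

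Quality of life is rated by patient and parent, and symptom severity by patient, parent and teacher. All of them would know the arm when they give the discharge rating. If the news changes that rating in one arm, the change enters the contrast that is meant to show the aftercare effect.

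The expectation item is more exposed still, because it names the programme. A family that knows it will have six video calls and a family that knows it will have usual aftercare are answering different questions. The variable then partly measures allocation, and an efficacy model that adjusts for it can remove part of the effect under study.

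**Working it through.** **1. Timeline, in days from discharge.** The figures in the article are not visible here, so this uses the text and Table 1.

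- Disclosure to family and teacher: about day -14 (briefing, with the start of the ambulatory assessment).
- Discharge and expectation questionnaires: day -7 to day 0.
- Gap: -7 - (-14) = 7 days at the least, 0 - (-14) = 14 days at the most.

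The windows do not overlap. The heading over the discharge column in Table 1 agrees.

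**2. How a reaction enters the contrast.** Score each outcome so that higher is better. Let τ be the true aftercare effect, s the between-arm difference at discharge caused by knowing the assignment, and s′ the part of it still present later.

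- Change from discharge estimates (τ + s′) - s.
- A passing reaction (s′ = 0) gives τ - s.
- A lasting reaction (s′ = s) gives τ, so it cancels.
- Change from admission estimates τ + s′, so a lasting reaction counts in full as an aftercare effect.

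Relief in the intervention arm or disappointment in the control arm makes s positive. A passing reaction then lowers the estimate.

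**3. Illustrative size.** The planned 25 per group cannot be reproduced, because the article gives no alpha, power, effect size or SD. The point does not depend on it. Assume two-sided alpha 0.05, a passing reaction, τ = 0.5 SD and correlation ρ between time points. For a simple change-score comparison:

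- SE = √(2(1-ρ)) × √(2/25), which is 1.000 × 0.283 = 0.283 at ρ = 0.5 and 0.775 × 0.283 = 0.219 at ρ = 0.7.
- Power ≈ Φ((0.5 - s)/SE - 1.96).
- Example, ρ = 0.5: s = 0 gives Φ(1.768 - 1.96) = 42%; s = 0.2 gives Φ(1.061 - 1.96) = 18%.

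| s (SD) | power, ρ = 0.5 | power, ρ = 0.7 |
|---|---|---|
| 0 | 42% | 63% |
| 0.1 | 29% | 45% |
| 0.2 | 18% | 28% |
| 0.3 | 10.5% | 15% |

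For scale, 25 per arm detects √(2/25) × (1.96 + 0.84) = 0.79 SD with 80% power, if the SD of the analysed score is 1.

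**4. Expectation.** If allocation moves expectation by 0.5 SD and expectation has a slope of 0.3 on the outcome, adjustment removes 0.5 × 0.3 = 0.15 SD of the group difference. Halving either input gives 0.075 SD. Both inputs are assumptions.

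**The case against.** **The reaction may last.** In an open trial, knowing the group may colour every later rating too. A lasting shift cancels in change from discharge; a simulation with a lasting 0.3 SD shift (25 per arm, correlation 0.5, no aftercare effect) rejected in 5.3% of runs. This stands, and it confines the concern to reactions that are stronger at discharge than later. It also shows why the admission value should not simply replace the discharge value: it would take a lasting reaction for an effect, and it precedes an inpatient stay averaging three months.

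**False claims of benefit.** A reader might infer that early disclosure inflates these. On the relief or disappointment reading it does the reverse. With a 0.3 SD shift at discharge and no aftercare effect, rejections in favour of the intervention fell to 0.4% in simulation, against 2.3 to 2.4% without a shift. A false benefit would need the intervention arm to rate itself worse at discharge because of its assignment. The plan also asks for post hoc tests to locate the interaction.

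**Which baseline.** The Abstract and Background count admission among the pre-post-follow-up time points, and the data security section puts admission and discharge together under pre-assessment. Admission may therefore already be a level of the ANOVA. Table 1, however, attaches the label to discharge alone, and a distorted discharge level enters the interaction either way.

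**Expectation adjustment.** A reader might infer that the primary models adjust for it. Statistical analyses names only group, time point and their interaction as ANOVA predictors. What stands is that the variable is declared "expectation of change regarding the aftercare is assessed as a covariate", with no earlier value and no statement of which models use it.

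**Discharge date.** A reader might infer that therapists who know the arm shift the date. The documents do not support this. An assessment that starts two weeks before discharge presupposes a planned date, and nothing says allocation can move it.

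**Conclusion.** The order of events is established by the article's own text: family and teacher are told 7 to 14 days before they complete the discharge questionnaires. This affects the discharge reference for two of the four primary outcomes, and the expectation covariate. Satisfaction is measured only after the aftercare and readmission has no baseline score, so neither is touched in this way.

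The harm is conditional. It needs a reaction to the assignment that is present at discharge and fades later. Its likelier form is a masked benefit. Size and direction cannot be derived from the documents, and the power figures rest on assumed shifts, an assumed effect and assumed correlations.

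This is a low-cost improvement worth making, not a flaw that invalidates the comparison. The early disclosure is avoidable, and once a discharge score has been given with the group known, no analysis can recover the score that would have been given without that knowledge.

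**What to change.** 1. Keep the technical briefing at the start of the ambulatory assessment, but do not reveal the group there. The article's list of components explained is not split by group. If the video or messenger parts are in practice shown to one arm only, move them to the later contact or show them to everyone.
2. Disclose the assignment to family and teacher once the discharge and expectation questionnaires are returned, or at discharge at the latest. Notify the therapist as late as scheduling allows.
3. State that efficacy models are not adjusted for expectation measured after disclosure. Analyse it as a possible mediator.
4. For patients already enrolled, keep the discharge reference and report a sensitivity analysis using the admission value for quality of life and symptom severity, which Table 1 lists ahead of allocation. State which time points the main ANOVA contains.

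**Cost.** There is less notice for arranging the first video and teacher calls, and a short second contact is needed to disclose the group. Late questionnaires could delay disclosure, hence the limit at discharge. At the stated version date (29 October 2021) recruitment was expected to run to June 2022, so items 1 and 2 could help later participants. Items 3 and 4 change wording and analysis only.

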### Interventions

In a naturalistic parallel group study design, DigiPuR compares a new digitally supported aftercare in the intervention group with TAU aftercare in the control group (see Fig. 2). Aftercare is provided in both groups, with aftercare in the control group being the same as the procedure for non-participation (i.e., TAU). Case-leading therapists working in the partial or full inpatient sector conduct the aftercare in both groups but are otherwise not involved in planning and evaluating the study. Documentation of aftercare appointments in both groups is handled digitally by the case-leading therapists using predefined input fields on relevant aspects in the hospital’s internal software programs. For both aftercare treatments following the partial or full inpatient stay, no additional risks are to be expected. There is no anticipated harm and no compensation for participating in the study. If there are any queries or complaints about the study or the data management, participants can contact the appropriate study-independent office by e-mail or telephone at any time using the contact details on the participant information form. DigiPuR study staff work in the research department and are at no time involved in the therapeutic process, but are contact persons for questions regarding, for example, technical difficulties of participants or the case-leading therapists.

**Fig. 2 Fig2:**
[figure not shown]
Time schedule of the study for both groups. 

= video/phone call. 

= messenger 

= aftercare appointment at the hospital

#### Intervention group

In the intervention group, children and adolescents take part in six video calls with the case-leading therapist of the previous partial or full inpatient hospital treatment. These video calls take place weekly during the first 4 weeks after discharge, then every 2 weeks until 8 weeks after discharge and last up to 50 min, depending on the individual needs of the patient as determined by the therapists. Participants take part in these six video calls from their homes. The case-leading therapist decides whether parents and, if required, responsible persons from external support systems such as youth services, outpatient psychotherapists, psychiatrists, and pediatricians also participate in the video calls. Content of the video calls depends on the case and is linked to previous partial or full inpatient behaviorally oriented psychotherapy with focus on transfer of learned strategies into daily routines. A weekly goal is worked out with the child or adolescent in each video call and written down on a worksheet so that its achievement can be assessed retrospectively at the next session. The case-leading therapist deciding on duration, participants, and content allows the aftercare program to be sufficiently flexible and well adapted to the needs of the patients. Reducing the frequency of aftercare from weekly to biweekly video calls aims to gradually strengthen the patient’s autonomy and allows support in the home environment with personal contact to the therapist, but without time-consuming and costly travel time.

The child’s or adolescent’s and parents’ agreement provided, additionally one or more teachers from the child’s or adolescent’s school participate in up to three 30- to 45-min video or telephone calls, separate from the family’s appointments, with the hospital’s case-leading therapist in the period up to 8 weeks after discharge. The German handbook *Psychische Erkrankungen im schulischen Umfeld* (Mental disorders in the school environment) is intended to support teachers additionally by providing information and support beyond the three calls. We developed this handbook primarily for schools in the state of Baden-Wuerttemberg, Germany in response to the internally identified needs of teachers for more knowledge about mental disorders and how to deal with students with mental disorders. It covers the following topics: (1) knowledge about mental disorders, (2) dealing with mental disorders in daily school life, (3) returning after a psychiatric hospitalization, (4) dealing with mental emergencies, (5) finding an appropriate attitude, (6) hints for talking to affected students, (7) taking care of yourself, and (8) school programs for health promotion (publication of the handbook is planned after the end of this study; for more information, please contact the corresponding author). The contents of the handbook are possible subjects of video or telephone calls with teachers, with different key aspects depending on the specific case.

All children or adolescents, parents, and teachers in the intervention group can send a direct message via messenger function to the case-leading therapist via the app *movisensXS* [49], individualized by the authors as the PANDA-App (Psychiatrische Aufenthalte – Nachsorge Durch App, Psychiatric Stays – Aftercare Through App). Messages can refer to, for example, content issues or organizational matters, but do not contain personal data such as names or locations due to data security restrictions. The case-leading therapists receive these messages via their professional e-mail address and can reply to messages in the browser after logging in to the Movisens platform. This messenger service must, however, not be used for emergency contacts, as those must be made via the regular emergency number of the responsible hospital.

#### Control group (TAU)

In the control group, children and adolescents and their parents are usually given a 50-min follow-up consultation with the case-leading therapist from the previous partial or full inpatient treatment in the hospital about 6 weeks after discharge. This corresponds to the usual aftercare treatment (TAU) in the Department of Child and Adolescent Psychiatry, Psychosomatics and Psychotherapy at the University Hospital of Psychiatry and Psychotherapy Tuebingen, Germany.

### Evaluation

Evaluation of DigiPuR includes a pre-post-follow-up assessment and an ambulatory assessment phase (see Fig. 2). All assessments are carried out in the same manner for the intervention and the control group. Adherence of participants regarding the assessment data is continuously and timely monitored by checking the return of questionnaires and the documentation of aftercare appointments. In case of multiple missing data, study staff inquire by phone. There are weekly project meetings to discuss trial conduct and progress. Internal reports document and provide information on project progress on a quarterly basis. As the trial is a low-risk intervention, there is no trial auditing.

#### Pre-post-follow-up assessment

Admission and discharge assessment as part of the standard hospital assessment are carried out on paper questionnaires (in exceptions where necessary online) through trained staff during the partial or full inpatient hospital stay in the period from preliminary talk to admission until 1 week after admission and in the period from 1 week before discharge until discharge (pre). For the post, follow-up 1, and follow-up 2 assessment (8, 24, and 36 weeks after discharge), the participants receive an e-mail containing a link for an online survey on the SoSci Survey platform [50], which they can respond to at home via the browser of their computer, tablet, or smartphone within 1 week. At each time point of assessment, the survey lasts no longer than about 45 min.

